### Study setting

This is a multicenter research project that will be conducted at a total of 21 research sites throughout Sweden. Organizations have naturally self-selected to either implement My Choice–My way! (*n* = 12) or to continue providing Usual Services (US, *n* = 9). All twelve organizations that implement My Choice—My Way! are part of the Swedish social services, although some are public and others private providers of services to youth. The nine organizations that constitute the control group and provide US are various organizations that provide support for the target group either within the Swedish social services or as a part of civil society. A list of study sites can be obtained from the first author of this protocol.

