### Sample size

Following Cohen’s proposed interpretation of *f*, this study will need a minimum of 124 youth to fully participate (complete) in the effectiveness trial in order to test within and between interactions over three measurement points [54, 55]. Assuming a 20% drop out rate, we aim to recruit 80 youth per study arm. This will result in 85% statistical power to detect a medium (*f* > .25) effect with alpha set at .05 for a repeated measures ANOVA with within and between interactions.

Service provider sample size is based on the ratio of service provider to youth participant referred to the study.

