### Allocation

This study will follow the natural assignment of youth to condition (i.e., the research team will not manipulate the normal operating procedures of the participating municipalities/organizations but instead will follow youth as they are assigned to My Choice–My Way! and US). We will implement a rolling inclusion. Youth will be admitted to the study as they are referred to one of the study arms (My Choice–My Way!, US). Inclusion to the study will continue until we have included the desired number of participants.

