### Statistical methods

#### Aim 1 statistical methods

*Baseline characteristics*. Demographic/background and T1 values on outcome variables will be investigated for the entire group and each arm separately.

*Baseline differences in between-group analyses*. Baseline differences on background and outcome variables between groups at T1 (due to the absence of randomization) will be investigated (e.g., *x2*, *t*-test, Mann-Whitney U). Any identified differences will be statistically controlled for in between group analyses.

*Attrition*. Analysis of within group and between group attrition will be conducted (i.e., differences in baseline characteristics of those that remain in study and those that drop out e.g., *x2*, *t*-test, Mann-Whitney U).

*Intent-to-treat (ITT)*. All analyses will be conducted with an ITT approach and missing values on follow-up data will be imputed using the maximum likelihood (ML) approach.

*Sensitivity analysis*. All results will be investigated through sensitivity analysis for their robustness to assumptions and method choices made during the course of the study (e.g., results with imputation vs results without imputation, changes in resource use and cost data).

*RQ1*. The relative effectiveness of My Choice–My Way! and US will be assessed by analyzing within group and between-group changes on participant self-reported and register data after T2 and again after T3 data collection using e.g., ANOVA, ANCOVA depending on final data characteristics.

*RQ2*. Participant characteristics measured at T1 (e.g., gender, age, type of placement) to will be analyzed (e.g., regression-based moderation analysis, ANCOVA depending on final data characteristics) for their moderating effect on changes in self-reported and register data collected at T2 and T3.

*RQ3*. Service provider reported implementation measures (i.e., acceptability, appropriateness, feasibility) and fidelity scores from the systematic session observations will be analyzed (e.g., regression-based moderation analysis, ANCOVA depending on final data characteristics) for their moderating effect on changes in participant self-reported and register data collected at T2 and T3.

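### Arm is set by organisation (12 vs 9 self-selected sites), but the stated 85% power makes no allowance for clustering and the tests named for RQ1 take youth as independent

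*Protocol article*

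**What the plan says.** Study setting describes "a total of 21 research sites throughout Sweden" and says "Organizations have naturally self-selected to either implement" the programme (12 sites) or to carry on with usual services (9 sites). Under Allocation, the researchers leave each organisation's normal procedures alone: "Youth will be admitted to the study as they are referred to one of the study arms". No section describes a site that delivers both arms.

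The Sample size section states that "this study will need a minimum of 124 youth to fully participate (complete) in the effectiveness trial"; this number is tied to a test that uses all three questionnaires. With 20% dropout the aim is 80 youth per arm, which is said to give 85% power for a medium (f of .25) "effect with alpha set at .05 for a repeated measures ANOVA with within and between interactions". No ICC, design effect or number of sites enters this statement.

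Under Aim 1 statistical methods, RQ1 compares changes within and between groups "after T2 and again after T3 data collection using e.g., ANOVA, ANCOVA depending on final data characteristics". The only adjustment is for baseline differences between the arms. No section mentions a site term, a multilevel model or cluster-robust errors.

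**The concern.** The arm contrast is a comparison of 12 organisations with 9 others. Youth at one site share staff, local services and case mix, so their outcomes may be correlated. Because arm does not vary within site, any such correlation in the quantity being compared adds to the variance of the arm effect. A youth-level ANOVA or ANCOVA does not see that extra variance, and adjusting for youth baseline differences does not supply it.

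At stake is the test of H1, the main effectiveness hypothesis. Differences between sites in how youth develop could be read as a programme effect more often than the nominal 5%, and the power on which recruitment rests could be lower than stated.

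**Working it through.** **Inputs.** From Sample size: 124 completers, 20% dropout, 80 per arm, f = 0.25, alpha 0.05, power 85%, three measurements. From Study setting: 12 and 9 sites. Assumed, because the article gives no value: ICC 0.01 to 0.10, equal or near-equal site sizes, and the correlations stated below.

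**Step 1: the plan's own figure.** Dropout is consistent: 124/0.8 = 155, below 160, and 160 × 0.8 = 128 completers. The 85% cannot be confirmed, since it depends on an unstated correlation rho between measurements. With N = 124 and independent youth:
- Between-group effect, lambda = f²·N·3/(1+2·rho): 85% at rho of about 0.77, 92% at rho 0.5.
- Group-by-time interaction, lambda = f²·N·3/(1−rho): above 99% already at rho 0.
- Group-by-time interaction, lambda = f²·(N−2)·2: about 94%.

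None of these has a cluster term.

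**Step 2: design effect.** The 62 completers per arm give 62/12 = 5.17 and 62/9 = 6.89 per site. The design effect (DE) is the mean over arms of 1+(m−1)·ICC. At ICC 0.05: (1.208 + 1.294)/2 = 1.25.

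**Step 3: power, if 85% is the unclustered power of a 1-df arm contrast.** Divide the noncentrality by DE and use 21−2 = 19 df.

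| ICC | DE | Power, large df | Power, 19 df | Completers needed (124 × DE) |
|---|---|---|---|---|
| 0 | 1.00 | 85% | 82% | 124 |
| 0.01 | 1.05 | 83% | 80% | 130 |
| 0.05 | 1.25 | 76% | 73% | 155 |
| 0.10 | 1.50 | 69% | 65% | 186 |

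The last column allows for DE only; the 19 df would add more. With 128 completers, power on 19 df is 81%, 74% and 66% at ICC 0.01, 0.05 and 0.10. About 3 points of the loss come from the 19 df alone.

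**Step 4: the same design effects under the interaction formulas.** With 124 completers and 38 denominator df:
- lambda = f²·N·3/(1−rho): 93% at ICC 0.10 with rho 0, and above 99% with rho 0.5.
- lambda = f²·(N−2)·2: 92%, 86% and 79% at ICC 0.01, 0.05 and 0.10.

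**Step 5: type I error of the youth-level test at nominal 5%.** Simulation with no true effect, 64 per arm, 12 vs 9 near-equal sites, youth-level correlation 0.5 between T1 and T2, 20,000 runs per setting:

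| Correlation of site effects, T1 to T2 | ICC | Change score | ANCOVA |
|---|---|---|---|
| 0.5 | 0.01 | 5.8% | 5.7% |
| 0.5 | 0.05 | 8.1% | 8.0% |
| 0.5 | 0.10 | 11.3% | 11.2% |
| 1.0 (fully stable) | 0.05 | 4.8% | 5.7% |
| 1.0 (fully stable) | 0.10 | 4.9% | 6.7% |

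In a separate simulation of a single-time comparison with 124 completers, the youth-level test rejected in 8.3% and 11.4% of runs at ICC 0.05 and 0.10. A t-test on the 21 site means stayed below 5%.

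**The case against.** **The RQ1 tests are only examples.** The wording leaves room for a mixed model, and an analysis plan that is not shown may specify one. This stands as a limit: the type I figures apply to ANOVA or ANCOVA as named, and a reader who inferred that the trial's p-values will necessarily be too small would go beyond the article. It does not cover the Sample size section, which fixes a power figure for a named youth-level test. The nesting is also known now and need not wait for the data.

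**RQ1 is about change, so stable site differences largely cancel.** This stands. The relevant quantity is the between-site variation in change. With fully stable site effects the change-score test holds its level and ANCOVA is only slightly above it (Step 5).

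**The power loss is not demonstrated.** This stands in part. One might infer that the design lacks 85% power, but Step 4 shows that some interaction conventions stay above 85% at ICC 0.05. What remains is that the stated figure carries no allowance for clustering.

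**Arm by site is an inference.** Allocation speaks of youth being referred to an arm, and the eligibility section adds an individual condition for the programme. Study setting, however, places each organisation in one arm or the other. A site offering both would weaken the clustering of arm at that site, but none is described.

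**Conclusion.** The concern holds conditionally. Arm is an organisation-level exposure with 21 clusters, and neither the power statement nor the RQ1 tests as named reflect this. If sites differ in change over time, the named tests understate the standard error of the arm effect. Type I error is then about 8% to 12% for an assumed ICC of 0.05 to 0.10 with moderately correlated site effects, and close to 5% if site effects are fully stable or the ICC is about 0.01.

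The fall from 85% to about 80%, 73% and 65% holds only if 85% is the unclustered power of a 1-df arm contrast. The article does not give the correlation needed to decide that. The ICC range is an assumption throughout. Markedly unequal sites, or further clustering by service provider, would raise the design effect.

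**What to change.** **RQ1 analysis.** Analyse T2 and T3 adjusted for the T1 value, with a random organisation effect on the follow-up outcome. Alternatively, use a T1–T3 mixed model with both organisation and organisation-by-time random effects. Use Kenward-Roger or Satterthwaite df, about 19 for the arm contrast. A random organisation intercept alone in a T1–T3 model is not enough: it does not absorb site variation in change, so the arm-by-time test would stay anti-conservative in the case that matters. A baseline-adjusted site-level analysis, or cluster-robust errors with a small-sample correction, would also serve.

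**Sample size.** State the powered effect and the assumed correlation between measurements. Replace the unqualified 85% with the power for that effect over an ICC range such as 0.01 to 0.10.

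**Cost.** A wider confidence interval and a less favourable stated power. No new data or enrolment is needed, provided each youth's recruiting organisation is recorded. The change corrects the error bars; it does not address confounding from self-selected sites.

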***Participation in Education*** (*sv*. Registerbaserad AKtivitetsStatistik) is a national registry database held by Statistics Sweden (https://www.scb.se/vara-tjanster/bestall-data-och-statistik/bestalla-mikrodata/vilka-mikrodata-finns/individregister/registret-over-befolkningens-studiedeltagande/). The statistics are based on registers for students in upper secondary school, adult education, qualified vocational education, labor market education and university and college. The information contained in this database enables the ability to describe the type of education, place of study, existence of study grants or loans, and educational provider for each individual within the study.

***Criminality*** is a combination between two ntional registry databases (*sv*. Belastningsregistret and *sv*. Misstankeregistret) held by the Swedish Police (https://polisen.se/lagar-och-regler/behandling-av-personuppgifter/polisens-register/). The registers contain information on whether a person has had criminal convictions, approved penalty orders and administrative fines, but also if they have been reasonably suspected of a crime or have been requested to be surrendered or extradited for a crime (with the exceptions of traffic violations). Only individuals over the age of 15 can be included in these registers.

***Hospital care*** derives from the national Patient registry (*sv*. Patientregistret) held by the National Board of Health and Welfare (https://www.socialstyrelsen.se/statistik-och-data/register/patientregistret/). The register contains both an individual´s outpatient and inpatient care. The registry contains variables such as duration of care, type of care, care disruption, diagnoses, and medication.

Register data will be collected 24 months after T1 for all youth who have consented to participate in the study, regardless of whether they have completed T2 and T3 or not.

*Service provider level implementation measures*. Service providers delivering *My Choice–My Way*! fill out the following implementation outcome measures post T2 based on Weiner et al. [53] on 5-point Likert scales: Acceptability of Intervention Measure (AIM, 4 items), Intervention Appropriateness Measure (IAM, 4 items), and Feasibility of Intervention Measure (FIM, 4 items).

Intervention dose estimation framework and tool assess intervention duration, percentage of intervention delivered, number of sessions (3 items).

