### Data collection methods

Youth level data will be collected through a digital questionnaire at three (i.e., T1, T2, T3) time points. First, pre-test measurements (T1), directly following the informed consent procedure but prior to program start. Post-test measurement (T2), after completion of My Choice–My Way! (approximately 8 months after T1, standardized across groups). Third, follow-up measurements (T3), 9 months following T2. Youth level register data will be collected 24 months after T1.

Upon declaration of interest to participate in the study, the youth will be given the option to give their informed consent and fill in the baseline questionnaire electronically via a link received through e-mail or over the phone with a member of the research team. Each youth who chooses to participate will receive compensation for their time upon filling out each questionnaire (approximately $20). Participants are able to choose between receiving compensation in cash or in the form of a gift card.

Service providers of My Choice—My Way! will be asked to complete a questionnaire post-T2 data collection investigating key determinants of implementation success.

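### The RQ1–RQ3 analyses place register data at T2 and T3, but the protocol collects them once, 24 months after T1, and states no reference periods for the change

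*Protocol article*

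**What the plan says.** The protocol article gives the timing of register data in two ways.

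**Collection.** The section on other outcomes says "Register data will be collected 24 months after T1 for all youth who have consented to participate in the study", whether or not a youth completed T2 and T3. The data collection section repeats it: "Youth level register data will be collected 24 months after T1". No other register collection is mentioned.

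**Meaning of T1, T2 and T3.** These are questionnaire occasions: "Youth level data will be collected through a digital questionnaire at three (i.e., T1, T2, T3) time points". T2 is "approximately 8 months after T1, standardized across groups". For T3 the text reads "Third, follow-up measurements (T3), 9 months following T2".

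**Analysis.** Under Aim 1 statistical methods:
- RQ1 examines "changes on participant self-reported and register data after T2 and again after T3 data collection".
- RQ2 tests T1 characteristics "for their moderating effect on changes in self-reported and register data collected at T2 and T3".
- RQ3 tests implementation and fidelity measures as moderators of "changes in participant self-reported and register data collected at T2 and T3".

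The trial design section describes the register component as a longitudinal register study of long-term outcomes. The baseline paragraph under Aim 1 says that T1 differences on background and outcome variables will be controlled for in between-group analyses.

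**The concern.** The analysis text treats register data as if they arrived with the questionnaires at T2 and T3. The collection text says they arrive once, later than both. An analyst following RQ2 or RQ3 literally would look for register data sets that the collection schedule does not produce. RQ1 also implies a register analysis linked to T2, before anything has been retrieved.

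All three questions concern changes. A change in a register outcome needs a defined starting period and a defined end period. For questionnaire scales these are the T1, T2 and T3 answers. For register outcomes the text ties the end periods to occasions when no register data are collected, and says nothing about which period stands for baseline.

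Two things make this worth settling. Education and employment are two of the programme's four stated outcome areas, and none of the listed self-report scales measures them directly; the registers do. Register data are also sought for every consenting youth, so they are not exposed to questionnaire dropout. In addition, organisations chose their own arm and youth are assigned by normal practice. A difference between arms in convictions, hospital care or study participation could therefore partly reflect differences present before enrolment, unless earlier register history is brought into the model.

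**Working it through.** **Inputs, all from the protocol article**
- T2: about 8 months after T1 (data collection methods)
- T3: 9 months after T2 (data collection methods)
- Register collection: 24 months after T1 (other outcomes; data collection methods)
- Recruitment: 2 October 2022 to a prospective end on 31 December 2023 (participant timeline)

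**Step 1. Timeline for one youth**
- T3 = 8 + 9 = month 17
- Collection minus T2 = 24 − 8 = 16 months
- Collection minus T3 = 24 − 17 = 7 months

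Register collection coincides with neither T2 nor T3.

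**Step 2. Does rolling inclusion rescue the analysis after T2?**
- Last T2 = 31 December 2023 + 8 months = about 31 August 2024
- First month-24 date = 2 October 2022 + 24 months = 2 October 2024

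The last T2 falls about one month before the first youth reaches month 24. A register analysis done promptly after T2 collection closes would have no collected register data for anyone. If recruitment ran past about 2 February 2024 (2 October 2024 − 8 months), the earliest youth would have reached month 24 by the last T2, but later enrolees would not.

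**Step 3. The analysis after T3**
- Last T3 = 31 August 2024 + 9 months = about 31 May 2025
- Youth at month 24 by then: those enrolled by about 31 May 2023
- Not yet at month 24: those enrolled June to December 2023, the last 7 of 15 recruitment months
- Last month-24 date = 31 December 2023 + 24 months = 31 December 2025

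An analysis soon after the last T3 would have only part of the register data. One run after the end of 2025 would have all of it, and would still be later than T3.

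**Step 4. Sections side by side**

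| Question | Register timing in the analysis text | Fit with one collection at month 24 |
|---|---|---|
| RQ1, first analysis | after T2 collection | Conflicts if run promptly after T2 |
| RQ1, second analysis | after T3 collection | Compatible if run after month 24 |
| RQ2 | collected at T2 and T3 | Conflicts |
| RQ3 | collected at T2 and T3 | Conflicts |

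The sample-size figures play no part in this point.

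**The case against.** The strongest reply is that a retrieval date is not a coverage period. The trial design section announces a longitudinal register study. The labour-market database is described as following a person's transitions over time, and the other registers hold convictions, suspicions and episodes of care. One retrieval at month 24 could contain records from before T1 and from around T2 and T3. This stands. A reader might infer from the timing that RQ1–RQ3 have no register data, or that no register baseline can exist. The documents support neither inference.

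Three further points have weight:
- RQ1 is worded more loosely than RQ2 and RQ3, and its second analysis fits month 24.
- Extraction windows are a detail that a condensed article may leave to the full protocol or analysis plan, and the baseline paragraph plans control of T1 differences on outcome variables without excluding register outcomes. It would be wrong to say that pre-existing differences will go unadjusted.
- Register data are listed among the other outcomes, so the primary and secondary outcomes are untouched.

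The objection does not remove the conflict. RQ2 and RQ3 say when the data are collected, and the collection sections say something different. The baseline paragraph cannot be applied to a register outcome until someone says which period supplies its T1 value.

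**Conclusion.** The conflict is real and lies in the current text. One register collection at month 24 cannot also be a collection at T2 and T3, which come about 16 and 7 months earlier. A register analysis run promptly after T2 would precede the first collection. That last statement assumes that recruitment keeps to its stated dates and that the analysis follows the last T2 without a long wait.

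The analyses can be rescued, because one retrieval may reach back over earlier periods. As written, though, the change to be analysed has no stated reference periods. The sections must be reconciled before data are ordered.

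The gain from adjusting for register history before T1 cannot be put as a figure, because the documents give no correlation between earlier and later register outcomes and no baseline difference between arms. The case for it rests on the non-randomised allocation. The point is of moderate weight: it should be corrected, but it does not affect the primary outcomes.

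**What to change.** 1. Rewrite RQ1–RQ3 so that the register analyses are run once, after the month-24 retrieval is complete for all consenting youth. Keep the T2 and T3 wording for the self-report data only.
2. State the register outcome period. Either use T1 to T1 + 24 months as one period, or name the retrospective windows within it that represent T2 and T3. Either choice resolves the conflict.
3. In the same retrieval, request the same variables for a period of fixed length before T1. Adjust the register models for these variables and for age.

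**Cost.** The changes are to wording, plus a longer window in an order that is already planned. The order may be slightly larger, and consent and ethics cover for the period before T1 must be checked.

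**Limit.** The youngest participants will have partly empty earlier history. Eligibility starts at 15, while the criminality registers hold only those over 15 and the education register as described starts at upper secondary school. Adjusting for age acknowledges this but does not supply the missing history, so the text should say how an empty period will be coded.

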### Objectives

The purpose of this project is to increase our understanding of how to promote the well-being across a spectrum of outcome areas for youth (15 + years old) transitioning from out-of-home care to independent living through the study of the implementation and provision of (A) My Choice—My Way! (*Swe*. Mitt val–min väg!) and (B) Usual Services. This includes an increased understanding of how interventions for this population can be designed, implemented, and sustained in diverse settings.

The project has five specific aims and eleven research questions.

#### Aim 1

To test the short- and sustained effectiveness of My Choice-My Way! in normal practice settings.

H1: Youth participating in My Choice-My Way! will exhibit gains in well-being and psychosocial outcomes relative to youth participating in Usual Services.

*Research questions*. RQ1 What is the relative effectiveness of My Choice-My Way! and Usual Services (US) for youth aged 15 and older in out-of-home care on well-being and psychosocial outcomes?

RQ2 How are outcomes moderated by subgroup characteristics?

RQ3 How does implementation fidelity moderate outcomes?

RQ4 What is the relative economic impact of My Choice–My Way!?

#### Aim 2

To advance our understanding of how specific behavior change techniques and theory-based change mechanisms impact youth outcomes.

H2: Theoretically based change mechanisms (e.g., experiences of success targeting self-efficacy change) will have a mediating effect on outcome (e.g., increased engagement in educational activities) in interventions with detailed program content.

*Research questions*. RQ5 How are the specific behavior change techniques used by social workers related to theoretical change mechanisms?

RQ6 How do the specific change mechanisms in transition services mediate youth outcomes?

#### Aim 3

To assess the extent to which implementation support (i.e., GTO) can impact fidelity and sustainability in practice settings.

H3: Organizations engaging in implementation support will exhibit increased fidelity relative organizations not engaging in implementation support.H4: Organizations engaging in implementation support will exhibit increased sustainability relative organizations not engaging in implementation support.

*Research questions*. RQ7 How does implementation support impact fidelity?

RQ8 How does implementation support impact sustainability?

#### Aim 4

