#### Service providers

Those who are selected by their organizations to deliver My Choice–My Way! to youth participants are referred to as service providers. There were no specific inclusion criteria other than that the organization finds this person to be suitable for delivering the support and the service provider has received the authorized training in My Choice–My Way! The service providers included in the study had different roles within their organization. One thing all service providers have in common is that they interact with youth placed in different forms of out-of-home care in their daily work. All social workers charged with delivering My Choice–My Way! undergo a four-and-a-half-day training prior to starting their work with youth.

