#### Systematic session observation

Two sessions per youth will be randomly selected in the My Choice-My Way! arm of the study. The service provider will make a video recording of themselves (i.e., no video recordings of youth participants) providing the session to participant youth. The recordings will be sent to the research team for analysis of fidelity to model based on a structured assessment instrument.

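### RQ3 calls fidelity and provider ratings moderators, but both exist only in the My Choice arm, so only an exploratory within-arm association can be estimated, and the post-T2 ratings cannot explain change up to T2

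*Protocol article*

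**What the plan says.** Under Aim 1, the effectiveness aim, the Objectives section asks: "RQ3 How does implementation fidelity moderate outcomes". The Aim 1 statistical methods answer it with "Service provider reported implementation measures (i.e., acceptability, appropriateness, feasibility) and fidelity scores from the systematic session observations", to be analysed "for their moderating effect on changes in participant self-reported and register data collected at T2 and T3". Regression-based moderation and ANCOVA are given as examples of method.

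Other sections fix where and when these variables arise:

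- **Session fidelity** (Systematic session observation): "Two sessions per youth will be randomly selected in the My Choice-My Way! arm of the study". The research team scores the recordings.
- **Acceptability, appropriateness and feasibility** (Other outcomes): providers delivering My Choice "fill out the following implementation outcome measures post T2". Data collection methods confirms the timing: My Choice providers "will be asked to complete a questionnaire post-T2 data collection investigating key determinants of implementation success".
- **Who counts as a provider** (Service providers): those chosen to deliver My Choice "to youth participants are referred to as service providers". On this definition the Usual Services arm has no raters.

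The Aim 1 methods apply an intention-to-treat approach to all analyses, impute missing follow-up values, and control for T1 differences between the arms. They do not limit RQ3 to one arm. RQ2, by contrast, uses moderators measured at T1.

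**The concern.** Moderation of a treatment effect means that the difference between arms varies with a third variable. That variable needs a value in both arms, and ideally one fixed before the outcome. The RQ2 moderators can meet both conditions. The RQ3 variables fail the first. The provider ratings also fail the second with respect to T2.

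At stake is what RQ3 may claim. A correlation among My Choice youth, reported as a moderating effect under an effectiveness aim, would suggest that better delivery makes the programme work better than usual services. The same correlation would arise if engaged youth were easier to deliver to and also improved more, or if providers rated the programme more kindly after youth had done well.

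**Working it through.** The article states no figure for RQ3, so there is none to reproduce. The checks concern estimability and the possible size of a false association.

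**Inputs.** From Sample size: 80 youth recruited per arm and 20% dropout, so 80 × 0.8 = 64 expected My Choice completers; alpha .05. From Study setting: 12 My Choice organisations. All correlations, loadings and intraclass correlations below are assumptions shown as ranges.

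**1. Estimability.** Take the model change = b0 + b1·arm + b2·M + b3·arm×M, where M is fidelity or a rating.

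- If M is set to 0 in Usual Services, then arm×M equals M for every youth. The design matrix has rank 3 of 4, and b2 and b3 cannot be separated.
- If only youth with an observed M are used, all are in the My Choice arm. The rank is 2, and the arm effect is lost as well.

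More youth do not change this. Nor does the planned imputation, which concerns follow-up data.

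**2. Confounding by youth responsiveness** (relevant to both kinds of measure). Let predictor and gain each load λ on responsiveness, with no direct effect. Their correlation is r = λ². By the Fisher-z approximation, the chance of two-sided significance is about Φ(atanh(r)·√(n − 3) − 1.96), with √61 = 7.81.

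| λ | r = λ² | atanh(r) × 7.81 | False significance |
|---|---|---|---|
| .4 | .16 | 1.26 | 24% |
| .5 | .25 | 1.99 | 51% |
| .6 | .36 | 2.94 | 84% |

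Simulation of the same set-up agrees: about 25%, 51% and 84%. With unequal links, engagement correlating .4 with change and .2, .4 or .6 with fidelity, simulation gives 9%, 25% and 49%. With no link at all it gives 4.9%, as it should.

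**3. Reverse causation** (provider ratings only). If ratings have no effect but correlate .1, .2 or .3 with change that has already occurred, simulated false significance is 11.5%, 35% and 67%.

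**4. Which outcomes are affected.** Data collection methods places T2 about 8 months after T1, T3 9 months after T2 (about month 17), and register collection at month 24. T1–T3 change equals T1–T2 change plus T2–T3 change, so a rating made after T2 still follows part of the T3 change from baseline. Register events dated before the rating have the same problem. T3 adjusted for the T2 value, and register outcomes dated after the rating, do not.

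**The case against.** The strongest reply is that RQ3 never mentions Usual Services. RQ1 and RQ4 ask about relative effects, whereas RQ3 asks only whether fidelity moderates outcomes, and the methods speak of changes. A fidelity-by-time analysis within the My Choice arm fits that text and can be estimated. This stands, so a reader who infers that RQ3 cannot be analysed at all goes too far. But RQ3 sits under an aim with a comparative hypothesis, the text states no within-arm restriction, and the within-arm reading still yields a non-randomised association with a post-assignment variable.

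Three further stronger readings are tempting and not supported:

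- **That all RQ3 measures are contaminated by timing.** Session fidelity is scored by researchers from recordings of randomly selected sessions, so the post-T2 objection does not apply to it. Even for the ratings, nothing says that providers see the youths' questionnaire scores. That they form impressions while working with the youth is plausible but inferred.
- **That youth will be analysed as independent.** The article does not say so. It gives methods as examples and may leave random effects to a fuller plan. The cost of ignoring clustering also depends on provider numbers, which are not given. At intraclass correlations of .05 to .20, the 5% error becomes about 7% to 16% if ratings are constant within 12 organisations, about 6% to 10% with 20 providers, and about 6% to 7% with 32.
- **That RQ3 drives the implementation conclusions.** H3 and H4 are tested separately under Aim 3, and RQ3 has no hypothesis of its own.

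**Conclusion.** The point holds in limited form. As collected, the RQ3 variables cannot show moderation of the My Choice versus Usual Services effect. This is exact and needs no assumption. They can show an association within the My Choice arm, which the article neither restricts to that arm nor labels as exploratory. For the provider ratings, using them to explain T1–T2 change puts the explanation after the outcome. For session fidelity, the concern is confounding by engagement, which the one stated adjustment (T1 differences between arms) does not address.

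The illustrative false-significance rates of about 25%, 51% and 84% rest wholly on the assumed loadings and on 64 completers. Weaker links give much smaller rates, down to 9% in the range shown. RQ3 is not the trial's main comparison, so this limits what RQ3 can conclude and leaves the principal result untouched. It is more than a detail for an analysis plan, because the article itself fixes the variables, the single arm and the timing.

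**What to change.** - State that RQ3 is restricted to the My Choice arm and reported as an exploratory association, without the term moderation.
- Adjust for the T1 value of the outcome, age, gender and type of placement, and allow for clustering by provider or organisation.
- Use the post-T2 ratings only for later outcomes: T3 adjusted for the T2 value, and register outcomes dated after the rating.
- Optionally, as a sensitivity analysis where caseloads allow, replace a youth's fidelity score by the mean over the same provider's other youth. This is undefined for a provider with one study youth and sets aside youth-level fidelity, so it should not be the main analysis.

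The change is one of wording and modelling and needs no new data. The cost is a weaker claim and a wider interval. With 64 youth and clustering ignored, power for a within-arm correlation is about 35% at .2, 68% at .3 and 81% at .35, so a null result for RQ3 would not be evidence that fidelity is unimportant.
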